**Figure 1 Study Diagram**

### 6.1.2 Follow-up amyloid PET Image visit

Participants assigned to the Early Amyloid PET arm will have an optional second amyloid PET scan (performed 12 to 18 months after the initial scan) and an additional study visit (within 28 days after the optional second scan). The change in amyloid load between scans will be quantified.

AEs that occur within 48 hours of study drug administration and all SAEs occurring within 30 days of study drug administration will be recorded.

## 6.2 Study Rationale

The study will compare the impact of early vs late utilisation of amyloid PET imaging on the etiologic diagnosis, diagnostic confidence, and clinical management of possible cases of AD.

This study's safety monitoring plan is justifiable and adequate from a safety standpoint. In view of the positive safety profile of these imaging agents, including the minimal radiation applied by the tracer administration and transmission scanning, the foreseeable risks to the participants and negative impact on the participant's well-being will be minimal and, when considering other diagnostic procedures involving radiation, is considered low.

## 6.3 Study Timeframe

- **Expected start of the study (first participant's first visit):** the fourth quarter of 2017.
- **Expected end of study (last participant's last visit):** the fourth quarter of 2020.
- **Final clinical study report:** the third quarter of 2021.

## 6.4 Risks and Benefits to Participants

### 6.4.1 Potential risks

This Phase 4 study uses radiopharmaceutical products whose safety and efficacy were established in Phase 1 to Phase 3 studies.

The potential risk of amyloid PET imaging is exposure to radioactivity from the tracer ( $[^{18}\text{F}]$ florbetaben or  $[^{18}\text{F}]$ flutemetamol). However, the tracer doses planned in this study are very low, and only 300 out of 900 patients will receive a maximum of 2 doses within 12 to 18 months. Dosimetry data derived from animals and humans indicate that potential radiation risks associated with studies using  $[^{18}\text{F}]$ florbetaben or  $[^{18}\text{F}]$ flutemetamol are low and comparable to those of other radio tracers [\[NeuraCeq™ SmPC\]](#)[\[Vizamyl SmPC\]](#). Specifically for this study, a maximum radiation dose of 6.1mSv/year will be administered. This ionizing radiation exposure is acceptable for the included subjects. The reasoning behind this is that, according to ICRP guidelines, the relative detriment for adults over 50 years of age is one fifth or one tenth of the 6.1mSv, the latter being based on radiation exposure of the whole population. As such, the relative dose for detriment assessment (corrected to adult dose) for a subject is between 0.61 and 1.22mSv, which is category IIa to IIb risk level for the volunteer. According to ICRP guidelines this is justified if the level of societal benefit is intermediate to moderate, which is the case of this study.

The recommended activity for an adult is 300 MBq ( $\pm 20\%$ ) for  $[^{18}\text{F}]$ florbetaben [\[NeuraCeq™ SmPC\]](#) and 185 MBq ( $+10\%$ ) for  $[^{18}\text{F}]$ flutemetamol [\[Vizamyl SmPC\]](#).

### 6.4.2 Potential benefits

We expect that amyloid PET imaging will help your clinician in having a higher confidence in his/her diagnosis regarding your condition, and in his/her prognosis and planning for your care management

The potential benefit to participants and treating physicians is knowledge about the participant's A $\beta$  status in the setting of cognitive impairment when the participant is undergoing evaluation for cognitive impairment possibly due to AD (SCD Plus, MCI or dementia).

- Demonstrating the absence of A $\beta$  pathology in participants with signs of cognitive impairment or dementia may facilitate a more accurate diagnosis and management, and a search for other, potentially reversible underlying aetiologies.
- On the other hand, knowledge of the presence of A $\beta$  may allow specific counselling on treatment interventions, prognosis, and planning.

It will be clarified that participation in the study will not prevent any currently available diagnostic option, but rather will give the opportunity to have access to the amyloid PET imaging, a diagnostic test approved by the European Medicine Agency but not yet reimbursed by most national health services.

### 6.4.3 Risk/benefit analysis

Previous studies consistently reported that amyloid PET imaging facilitates early identification of AD pathology and significantly enhances the specificity of diagnosis [Nordberg 2010]. The apparent minimal risk of the use of these radiolabelled imaging agents must be weighed against the benefit that A $\beta$  status has a significant impact on patient outcome and prognosis and allows targeted treatment intervention including a clinical management plan to be devised for an individual participant with better outcomes. The risks will be continuously monitored, assessed, and documented by the investigator.

Regarding potential benefits, individual patients can benefit from the study from a more accurate etiological diagnosis. In addition, participants can benefit whenever the diagnosis confidence after the PET scan increases, or when the etiological diagnosis is reached and/or management changes due to the results of the PET scan can be implemented. Moreover, future patients may benefit from this study as the appropriate use of amyloid PET in clinical routine to reach an etiological diagnosis might be expanded after this research is final.

If the risks will be found to outweigh the potential benefits or if there is conclusive proof of definitive outcomes, investigators will assess whether to continue, modify or immediately stop the study.

This information on risk and benefit will be conveyed to all participants (and their representative, if appropriate) verbally and in writing as part of the informed consent process prior to enrolment in the trial. In view of robust safety, tolerability, and minimal participant exposure of the drug substance and the clear medical need for tracers of this type, the low radiation risk appears justified.

## 7 SELECTION AND WITHDRAWAL OF PARTICIPANTS

### 7.1 Procedures for Enrolment

All consecutive patients coming to a participating Memory Clinic and their satellite centres with a request for diagnosis and appropriate age will be considered for the study. Some screening activities will be part of the clinical routine while others will be part of the clinical study. Written Informed Consent must be obtained before any study-specific screening procedures are performed.

### 7.2 Eligibility

Participants who fulfil all respective selection criteria and meet none of the exclusion criteria and satisfy the criteria for SCD Plus, MCI, or dementia where AD is in the differential diagnosis will be eligible for enrolment into the study. Written informed consent, which will be dated with time of consent noted, will be obtained from all participants. If necessary (i.e. in case of patient with dementia), written informed consent will be also obtained by the legal representative, and by a study partner, prior to study entry and prior to any protocol-specific procedures.

### 7.3 Inclusion Criteria

To be enrolled in the study, participants must meet all of the following criteria:

- The patient can be of any sex, gender, race, or ethnicity.
- SCD-Plus patients must be 60 to 85 years of age.
- Patients with MCI or with dementia must be 50 to 85 years of age.
- The patient must have a complaint (reported by the patient or by a caregiver) of cognitive problems that are considered by the managing physician to be possibly due to AD.
  - The patient must be entering a diagnostic assessment for the cognitive complaint.
  - The managing physician must feel that knowledge of the patient's brain amyloid status may increase diagnostic confidence and alter diagnosis and management.
  - Patients should not have known amyloid status prior to randomization.
- The patient must satisfy the diagnostic criteria for one of the following:
  - SCD-Plus (see Section 7.5.1)
  - MCI (see Section 7.5.2)
  - Dementia, where AD is in the differential diagnosis (see Section 7.5.3)
- The patient has undergone a dementia blood workup or will have one before amyloid PET.
- The patient has an MRI and/or CT scan (not older than 12 months) or will undergo one before amyloid PET.
- The patient can complete all clinical visits according to the protocol.
- The patient can tolerate a 20-minute amyloid PET scan.
- The patient (or, in case the patient is incapable of giving informed consent, next of kin or a legal representative as per national requirements) provides informed consent for study participation and data source verification. In case of a change in the capacity to consent, the local regulations will be applied. In case the patient is randomized to the Early Amyloid

PET arm, a new informed consent should be signed before the optional second imaging session.

- If the patient has dementia, a study partner is available for the duration of the protocol.
- In countries where patients unable of giving informed consent cannot be included in the study and an assessment of the patients' capacity to consent is requested, a study physician will assess the capacity to consent in patients with verifiable cognitive impairment prior to enrolment and regularly in the course of the study. If there are any doubts as to the patients' capacity to consent, the capacity to consent will be conclusively assessed by a specialist. Patients who are unable of giving informed consent, are excluded from the study in these countries.

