In all Arms, between Baseline visit and Week 12 visit, each time a biomarker is available, the result must be communicated to the managing physician, and the etiological diagnosis as well as the diagnostic confidence must be collected immediately. This will provide a sequential collection of diagnosis and diagnostic confidence up to Week 12 visit.

Amyloid load will be defined on the basis of visual reads at all time points. Only for the secondary aim of the disease modelling, amyloid load will be defined quantitatively. The results of the optional second amyloid PET scans (early amyloid PET arm) will be provided to the managing physician and may be used for clinical purposes.

The goal will be to enrol 100 participants per stratum in each arm, for a total of 900 participants.

Sites will be using PET-CT or PET-MR depending on what technology is available at each site.

Participation in the study will not prevent participants from having any currently available diagnostic investigation, but rather will give participants the opportunity to have access to amyloid PET imaging, a diagnostic test approved by the European Medicines Agency but not yet reimbursed by most national health services.

The study will comprise the following clinical visits and timepoints:

- A baseline clinical visit (Visit 0 [V0] at Time 0 [T0]), within 14 days after screening
- A timepoint 12 weeks after baseline (T1); no clinic visit is required at that time
- A clinical visit at 6 months  $\pm$ 14 days (V1 or T2), and
- An optional clinical visit at 13 months  $\pm$ 4 weeks (V2 or T3)

Amyloid PET imaging (conducted at the local sites and read visually) will not be considered a separate clinical visit.

At T1, the investigator will review the result communicated by the managing physician (if the investigator and the managing physician are not the same person) and record the etiologic diagnosis made by the managing physician, rate the managing physician's diagnostic confidence (0% to 100%, visual analogue scale [VAS]) as well as the managing physician's estimate of the likelihood that the patient's symptoms are due to AD (0% to 100%, VAS), and record the effective date of the managing physician's etiologic diagnosis and management plan. This does not need to be a clinical visit.

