| Lumbar puncture                                                          |   | (X)            |                | (X)            | (X)            |                | (X)            |   |   |
| Optional blood tests (eg, genetic testing)                               |   | (X)            |                | (X)            | (X)            |                | (X)            |   |   |
| Optional neuropsychologic testing                                        |   | (X)            |                | (X)            | (X)            |                | (X)            |   |   |
| Other                                                                    |   | (X)            |                | (X)            | (X)            |                | (X)            |   |   |

Brief COPE = Brief Coping Orientation to the Problems Experienced; CT = computed tomography; EQ5D-5L = EuroQoL 5-dimension questionnaire; MRI = magnetic resonance imaging;

Items in *italics* denote the clinical routine activities. (X) indicates diagnostic tests that are not mandatory and may be ordered at the managing physician's discretion; the results will be reviewed with the managing physician and patient at any following visit.

a Only the participants who are randomized to the Early Amyloid PET arm will undergo an optional second amyloid PET imaging scan 12 to 18 months after the initial scan and attend the T4 visit.

b Concomitant medications are recorded on the day of amyloid PET imaging.

c In order to be enrolled in the study, the participant must have had an imaging study (MRI or CT), not older than 12 months, to exclude intracranial mass or other lesions that might explain the cognitive impairment. Results must be available before enrolment.

d Randomisation will occur after all screening assessments are completed

e For the Early Amyloid PET arm, amyloid PET imaging will be done ≤4 weeks after T0 and again 12 to 18 months after the first imaging session. For the Late Amyloid PET arm, amyloid PET imaging will be done at 8 months (±8 weeks) after T0. If the managing physician chooses to order amyloid PET imaging for a participant in the Free-Choice Imaging arm, the imaging can take place at any time from T0 to 12 months after T0.

f Early Imaging arm,

g Late Imaging arm.

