- Review of current medications
- Physical examination
- Vital signs
- Height and weight
- Dementia blood workup, consisting in:
  - Complete blood cell count

- Serum electrolytes
- Glucose
- BUN/creatinine
- Serum B12 levels
- Thyroid function tests
- Liver function tests
- Evaluation of cognition/functioning (episodic memory, verbal memory, attention, verbal fluency, visual/spatial function, executive function)
- Results of brain magnetic resonance imaging (MRI) or computed tomography (CT) not older than 12 months before screening, showing the absence of an intracranial mass or other lesion(s) that might explain the cognitive impairment/complaint. Participants are eligible for the study only if these results are available.
- Managing physician's syndromic diagnosis
- The managing physician's estimate of the likelihood that the patient's symptoms are due to AD

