### **12.5.2 Statistical hypothesis, model, and method of analysis**

The difference between the Early Amyloid PET and Late Amyloid PET arms in the proportion of patients with an etiologic diagnosis in which the managing physician has  $\geq 90\%$  confidence at 12 weeks (the primary endpoint) will be evaluated with a chi-squared test with significance level of .05.

For each of the three strata (SCD Plus, MCI, and dementia) separately, the difference between the Early Amyloid PET arm and the Late Amyloid PET arm in the proportion of patients with an etiologic diagnosis with a confidence  $\geq 90\%$  at 12 weeks will be evaluated with a chi-squared test with an overall significance level of .05. The Bonferroni correction will be applied to control the family-wise type I error rate.

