## **12.6 Secondary Analyses**

### **12.6.1 Secondary efficacy variables**

In the analyses of the secondary efficacy variables, a cross-sectional difference between arms in a secondary endpoint at T1, T2, T3, or T4 (see Table 1) will be carried out by a chi-squared test if the endpoint is dichotomous, a 2-sided *t*-test if the endpoint is normal, and Mann-Whitney test if the endpoint is categorical or continuous and non-normal. The effect of baseline characteristics such as age, gender, MMSE, etc will be studied by a linear or logistic regression model.

A difference between study arms in the longitudinal change of a secondary endpoint will be tested by means of logistic or linear regression where the first measurement is a covariate (ANCOVA analysis) and the second measurement is the outcome. Differences in longitudinal

trends between arms will also be examined by means of the mixed-effects regression model. The effects of baseline characteristics such as age, gender, MMSE, etc. will be studied by including them in the regression models.

All tests will be 2-sided and the significance level will be set at 5%. Bonferroni corrections for multiple testing will be applied when appropriate. Point estimates will be presented together with 95% Wald confidence intervals. A 95% non-parametric confidence interval will be constructed if the estimate is non-normal.

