### 13.2 Ethical Considerations

To better evaluate the benefit of an early beta amyloid PET imaging in patients with SCD Plus, MCI, and dementia, the managing physician will be blinded to the other diagnostic test results for the Early Amyloid PET arm until their amyloid PET imaging results are available.

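### The protocol gives conflicting deadlines for MRI/CT and the dementia blood work-up; the one tied to the amyloid scan falls after the week-12 primary rating in the Late arm

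*Protocol*

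**What the plan says.** **Timing of MRI/CT and bloods.** Section 7.3 and the synopsis inclusion criteria state: "The patient has an MRI and/or CT scan (not older than 12 months) or will undergo one before amyloid PET" and "The patient has undergone a dementia blood workup or will have one before amyloid PET". Other places set an earlier point:

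- Table 1 lists MRI, CT and the blood work-up in the screening column. Footnote c says of the imaging: "Results must be available before enrolment". Footnote d places randomisation after completion of all screening assessments.
- Section 9.1 lists the blood work-up among the screening items recorded for every participant and says of MRI/CT: "Participants are eligible for the study only if these results are available".
- Section 10.3.8 has the imaging done in the 12 months before the screening visit.
- Section 10.3.24 describes the blood work-up as performed before participation, while also saying that the protocol requires no blood testing.

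**Disclosure of other results.** Section 13.2 states that "the managing physician will be blinded to the other diagnostic test results for the Early Amyloid PET arm" until the PET result is available. Section 9.2 lists baseline review of available FDG-PET, lumbar puncture and other results for the Late and Free Choice arms only. Section 6.1.1 (with the synopsis and section 9.4) requires, for all arms, that "each time a biomarker is available, the result must be communicated to the managing physician", with diagnosis and confidence collected at once.

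**The concern.** The primary endpoint is the managing physician's own confidence, cut at 90%, in an open-label trial. The Early-versus-Late contrast should reflect the amyloid scan and nothing else. If the work-up may wait until the scan, every Early patient scanned on schedule has structural imaging and bloods in hand by week 12, while a Late patient need have neither. The difference in proportions "will be evaluated with a chi-squared test with significance level of .05", and the specified test takes no account of which non-PET results the physician held. An imbalance would therefore be read as an effect of PET, in the direction of the hypothesis. A work-up missing at the week-12 rating cannot be supplied afterwards.

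The disclosure conflict is a separate matter. Sites following section 13.2 and sites following section 6.1.1 would collect different pre-PET ratings in the Early arm.

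**Working it through.** **1. The plan's own figures.** Section 12.7 gives power of more than 99%, 99.6%, 93% and 61% for differences of 25, 20, 15 and 10 points, with 300 per arm and 10% withdrawal.

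- Inputs: n = 300 × 0.9 = 270 per arm and two-sided alpha 0.05. The protocol gives no base rate, so proportions centred on 50% are assumed.
- Formula, with p̄ the mean of p1 and p2: power = Φ{[|p1 − p2| − 1/n − 1.96·√(2p̄(1 − p̄)/n)] / √[(p1(1 − p1) + p2(1 − p2))/n]}.
- Result: more than 99.9%, 99.6%, 92.7% and 61.0%. The stated powers reproduce, and this point does not dispute them.

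**2. Where the section 7.3 deadline falls.**

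- Early arm: PET within 4 weeks of baseline, so work-up by week 4. That is 12 − 4 = 8 weeks before the primary rating.
- Late arm: PET at 8 months ± 8 weeks. With 52.1775 weeks in a year, 8 months = 8 × 52.1775/12 = 34.8 weeks, so the window is weeks 26.8 to 42.8. Relative to week 12 the deadline is 26.8 − 12 = 14.8 to 42.8 − 12 = 30.8 weeks late.
- Under Table 1, 9.1, 10.3.8 and 10.3.24 the work-up comes at or before screening or enrolment in both arms, and the asymmetry vanishes.

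**3. Which text governs.** No precedence rule is stated. Section 9.1 sends the investigator to section 7.3 for the inclusion criteria, so the looser wording is the formal eligibility rule. The synopsis and section 6.1.1 give the Early scan priority over other diagnostic exams except MRI, which suggests that an MRI may still be outstanding after randomisation. The looser reading cannot be set aside as a leftover.

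**4. What an imbalance would do (illustration only).** Assume no true PET effect, 270 per arm, a two-sided test at 0.05, and a share f of Late patients who cannot reach 90% confidence at week 12 because the work-up is outstanding. Let p be the proportion otherwise reached. The spurious difference is f × p. None of these values is in the protocol.

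| f | Spurious difference (p = 0.2 to 0.5) | Rejection rate |
|---|---|---|
| 0 | 0 | 5% |
| 5% | 1.0 to 2.5 points | 6% to 9% |
| 10% | 2 to 5 points | 9% to 21% |
| 20% | 4 to 10 points | 23% to 65% |

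Worked cell, f = 0.10 and p = 0.5: 0.50 versus 0.45, difference 0.05. SE under the null = √(2 × 0.475 × 0.525/270) = 0.0430. SE under the alternative = √((0.25 + 0.2475)/270) = 0.0429. Upper tail: 1 − Φ[(1.96 × 0.0430 − 0.05)/0.0429] ≈ 0.21. The lower tail is negligible.

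**5. Does the disclosure rule reach week 12?** Section 13.2 lifts the withholding once the PET result is available. The scan is due by week 4, about 8 weeks before T1 less reading time. Section 9.4 then has other available results reviewed at T1 without distinction by arm. With an on-schedule scan the primary rating is not affected. What can differ by arm is the baseline rating (section 9.2 does not say whether it precedes the review of other results), the sequential ratings, time to a diagnosis at 90% confidence or more, and work-up cost.

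**The case against.** The best defence is that the two work-up rules can be met together. Tests done before enrolment are also done before PET, so a site following Table 1 and section 9.1 breaches nothing in section 7.3. More passages support the earlier timing than the later one. The SCD-Plus criteria in section 7.5.1 also exclude certain MRI lesions, and that diagnosis is made at screening. Table 1 marks these tests as clinical routine, so few patients may lack them 12 weeks into a diagnostic assessment. All of this stands, and it means that arm dependence follows from one of two conflicting texts and not from the protocol as a whole. It does not remove the conflict, because section 7.3 is the rule to which section 9.1 points.

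On disclosure, scanning first is a stated design feature, with a matching cost rule in section 10.1.2.3. Section 7.4 also excludes patients with earlier FDG-PET or CSF work-up unless the investigator is blind to the results until after randomisation. That narrows the conflict but does not reconcile section 13.2 with section 6.1.1.

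A reader might infer that withholding results in the Early arm also distorts the week-12 primary rating. The documents do not support this, because the withholding ends with the PET result. Any effect before then would, if anything, lower Early-arm confidence, opposite in direction to the work-up problem. The two act mainly on different endpoints and should be neither added together nor assumed to cancel.

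**Conclusion.** The point holds in limited form. The protocol contradicts itself on when MRI/CT and the blood work-up must be done, and one version puts the Late-arm deadline about 15 to 31 weeks after the primary rating. Where a site follows that version, the non-PET information behind the primary contrast can differ by arm, in favour of Early.

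The size cannot be derived from the protocol. The table above shows only that a modest imbalance could matter. It rests on assumed shares and on the extreme assumption that a patient without the work-up can never reach 90% confidence. A reader might infer that the primary result will be biased by some number of points; nothing in the document supports a particular number, or shows that any Late patient will lack the work-up.

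The disclosure conflict is real but of lesser weight. It concerns baseline and sequential confidence, time to diagnosis and cost, and not the week-12 primary rating when the scan is on schedule.

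**What to change.** 1. Reconcile the synopsis inclusion criteria and section 7.3 with Table 1 (footnotes c and d) and sections 9.1, 10.3.8 and 10.3.24. State one MRI/CT and blood work-up requirement that does not refer to the PET date and is identical in all three arms.
2. Report by arm, from the results already recorded in the eCRF, which non-PET results were available at the week-12 rating.
3. Reconcile sections 13.2 and 9.2 with the synopsis and sections 6.1.1 and 9.4 into one disclosure rule, stated once.

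The clinical content of both rules is for the sponsor to decide. The cost is a protocol clarification, a letter to sites and one descriptive table. An extra eCRF field is needed only if the dates on which results became available are not already captured. Sample size and the primary test are unchanged.
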